#### Intention-to-treat analysis

In general, all statistical analyses are performed by the intention-to-treat principle.

### Primary outcomes

#### Self-evaluation of questionnaire to identify the behavioral characteristics of mothers based on the educational program at 4 months after delivery

A linear mixed-effects model is used to analyze the total score of the questionnaire at 1, 4, and 12 months after delivery as an outcome variable. A mixed-effects model for repeated measurements (MMRM) [51] is used to properly handle missing values or dropouts that could arise during the study. An unstructured covariance structure is used to assess the correlation between outcomes at these time points. Mean changes from baseline are modeled as outcome variables for the MMRM. Mean changes from baseline at each time point are analyzed individually using a regression model. If the regression parameters cannot be estimated using the unstructured model, the covariance structure is changed in the following sequence: Toeplitz matrix model, heterogeneous compound symmetry model, autoregressive model (1), compound symmetry model, and variance components model. A primary analysis is performed using estimates for the regression parameter or regression parameter test at 4 months after delivery. The significance level is set at 5% (two-sided).

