### Measurements/assessments

#### Primary outcomes

##### Self-evaluation of questionnaire to identify the behavioral characteristics of mothers based on the educational program at 4 months after delivery

Primary outcomes are evaluated according to a self-evaluation score at 4 months after delivery in both arms.

The score is determined using a survey sheet created for this study (Appendix) to assess the behavioral characteristics of mothers. We prepared 21 questions to assess the dietary habits of mothers, living conditions, and the skin care of children based on the ideal behavior of mothers to prevent allergy in infant as proposed by specialists. Five options (a–e) are provided for all questions: a = 1, b = 2, c = 3, d = 4, and e = 5. Higher scores indicate more appropriate behaviors of mothers to prevent pediatric allergy at each time point.

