A questionnaire survey on living habits, awareness, and knowledge of mothers before and after pregnancy was prepared. Subjects answer the self-evaluation questions in the survey at 30 weeks of pregnancy, and at 1, 4, and 12 months after delivery. Questions on living habits address stool frequency, use of supplements, eating habits between meals, and foods avoided or foods eaten. Regarding awareness and knowledge, the questions address what the mothers care about before and after pregnancy, how they intend to provide nourishment for the baby, and their concerns regarding childcare and the skin care of the baby.
7.Adverse events

Self-reported adverse events associated with the use of the moisturizer provided free of charge to those who want to use it during the study are recorded.

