### Baseline characteristics

The baseline characteristics are evaluated at approximately 20 weeks of pregnancy. The variables to be measured include age; delivery experience; history and type of allergy of the subject, their partner, and siblings; type of pet, if any; and smoking status of the subject and her family members living together.

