### Participant timeline

Table 2 shows the consent forms obtained from the subjects, the intervention, and the evaluation schedule.

**Table 2 Tab2:** Consent, enrolment/allocation, and assessment of subjects (Additional file 2)

	Study period							
	Enrollment Allocation	Post allocation						
Time point	Early pregnancy	20 weeks of pregnancy	30 weeks of pregnancy	Delivery	Discharge	1 month after delivery	4 months after delivery	12 months after delivery
Enrollment/allocation:								
Inclusion	●							
Obtaining informed consent	●							
Randomization	●							
Baseline survey		●						
Interventions:								
Educational program		●	●					
Established childbirth education		●	●					
Assessments:								
Questionnaire survey on living habits, awareness, and knowledge of mothers before and after pregnancy			●			●	●	●
Survey on the behavioral characteristics of mothers						●	●	●
Blood collection from mothers	●		●					
Blood collection from infants (IgE and TARC)							●	●
Stratum corneum hydration of infants					●	●	●	
TEWL of infants					●	●	●	
Findings on the skin of infants (scoring atopic dermatitis (SCORAD)) [50]					●	●	●	
Images of the skin of infants					●	●	●	
Diagnosis of atopic dermatitis in infants							●	●
Diagnosis of food allergy in infants							●	●
Provision of moisturizer					●	●	●	
Collection of the moisturizer container						●	●	●

Legend: *IgE* immunoglobulin E, *SCORAD* scoring atopic dermatitis, *TARC* thymus and activation-regulated chemokine, TEWL transdermal water loss

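### The primary analysis names two incompatible response variables, and one of them, change from baseline, cannot be computed because the behaviour score has no baseline

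*Protocol article*

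**What the plan says.** All references are to the Protocol article.

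- **Definition of the primary outcome** (Measurements/assessments, Primary outcomes): "Primary outcomes are evaluated according to a self-evaluation score at 4 months after delivery in both arms". The score sums 21 items, each scored 1 to 5.
- **Analysis, first statement** (Statistical analysis, Primary outcomes): the mixed model's stated purpose reads "analyze the total score of the questionnaire at 1, 4, and 12 months after delivery as an outcome variable".
- **Analysis, second statement** (same paragraph): "Mean changes from baseline are modeled as outcome variables for the MMRM".
- **Analysis, third statement** (same paragraph): "Mean changes from baseline at each time point are analyzed individually using a regression model".
- **Primary test** (same paragraph): the regression parameter at 4 months, two-sided 5%.
- **Schedule** (Participant timeline, Table 2): the row "Survey on the behavioral characteristics of mothers" is marked at 1, 4 and 12 months after delivery and nowhere earlier.
- **Baseline** (Baseline characteristics): "The baseline characteristics are evaluated at approximately 20 weeks of pregnancy". The list reads "The variables to be measured include age; delivery experience; history and type of allergy of the subject, their partner, and siblings", and continues with pets and smoking status.

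**The concern.** A confirmatory analysis needs one response variable, fixed in advance. Here the opening sentence gives the total score, and the sentence that specifies the MMRM response gives change from baseline. The second needs a value of the same score from before the intervention, and the schedule provides none.

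An analyst who follows the paragraph literally must therefore choose the primary response outside the plan. The only route to a computed change would be to treat the 1-month score as the baseline. That score is taken after both education sessions, so subtracting it would remove any effect of the program already present at 1 month.

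**Working it through.** **1. Is there any baseline value of the score?**

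| Source | What it shows |
|---|---|
| Table 2, behaviour survey row | 1, 4 and 12 months after delivery only; no entry at enrolment, 20 weeks or 30 weeks |
| Baseline characteristics | Age, delivery experience, allergy history, pets, smoking; no behaviour score listed |
| Secondary outcomes, item 6 | A separate survey of living habits, awareness and knowledge: "Subjects answer the self-evaluation questions in the survey at 30 weeks of pregnancy, and at 1, 4, and 12 months after delivery" |
| Table 1, item 8 | Education sessions at about 20 and 30 weeks of pregnancy |

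The one questionnaire given during pregnancy is a different instrument. It is first given at 30 weeks, after the 20-week session. It cannot supply the baseline.

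**2. Could the score be obtained in pregnancy?** Item count from the Appendix, Table 3:

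- Mother or household: bed pad, bedclothes, smokers at home, own smoking, sunlight, sunscreen and six food items = 12.
- Born infant: taking the baby outside (1), washing (4), moisturizer (4) = 9.
- 12 + 9 = 21.

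Nine of the 21 items have no answer before birth, so the 21-item total could not be formed at 20 weeks.

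**3. Would the 1-month score serve?** Let d1 and d4 be the arm differences in mean total score at 1 and 4 months. The expected arm difference in the 4-month minus 1-month change is d4 − d1, not d4. At 1 month the change would be zero for every woman, although the paragraph lists 1 month as an outcome time.

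**4. The plan's own design figure.** Inputs from Sample size: 60 per group, SD 16, alpha 0.05, power 80%, t test.

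- Standard error of the difference: 16 × √(2/60) = 2.92.
- Detectable difference, normal approximation: (1.960 + 0.842) × 2.92 = 8.18; with the t distribution, 8.25.

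This reproduces the stated figure of about eight, read as a detectable difference. The section calls it a standard error of the mean, but the standard error of a group mean is 16/√60 = 2.07. The calculation is a plain two-group comparison with one SD and no correlation between visits, so it fits the total score at 4 months.

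**5. Are the two responses interchangeable for power?** Suppose a true baseline existed, with SD 16 at both times and correlation r. The documents give no r. The SD of change is 16 × √(2(1 − r)).

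| r (assumed) | SD of change | Detectable difference | Power for 8 points |
|---|---|---|---|
| 0.3 | 18.9 | 9.7 | 64% |
| 0.5 | 16.0 | 8.2 | 78% |
| 0.7 | 12.4 | 6.3 | 94% |

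The total score gives 78% for 8 points at the same sample size. The two match only at r = 0.5.

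**6. Illustration of a 1-month substitution.** Assume d4 = 8.25 and equal SDs of 16.

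- If d1 = 8.25, the expected change difference is 0 and the test rejects 5% of the time.
- If d1 = 6, the change difference is 8.25 − 6 = 2.25. With r = 0.5 the standard error is 2.92 and power about 12%. With r = 0.7 it is 12.4 × √(2/60) = 2.26 and power about 17%.
- The 4-month total score gives 80%.

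The values of d1 and r are chosen for illustration. Only the direction is general: whatever effect is present at 1 month is subtracted.

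**The case against.** The strongest reply is that a valid primary analysis is already in the text. The opening sentence of the analysis paragraph makes the total score the outcome, the outcome definition fixes the 4-month score, and the test is tied to the 4-month parameter at two-sided 5%. That model runs on the scheduled data. This stands. A reader might infer that the primary analysis cannot be run at all, or that the confirmatory test is undefined; the text does not support that. Only the change-from-baseline version is impossible.

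Four further points are fair:

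- No section proposes the 1-month score as a baseline, and listing 1 month as an outcome time argues against it. A reader might take the 5% to 17% power figures as the power of this plan. They are not; they describe a substitution that the documents do not make.
- The sentence on analysing each time point individually may mean the visit-specific parameters of the same MMRM. Separate regressions, and so a third analysis, are possible but not established.
- The baseline list is introduced as what the variables include, so it may not be complete, and Table 3 is titled as the 4-month form. This softens the wording only: no pregnancy version of the behaviour survey is documented, and Table 2 shows none.
- Table 2 places the baseline survey after allocation. The listed variables are mostly fixed history, and the primary model text does not use them, so this adds nothing here.

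An appeal to a separate analysis plan does not remove the problem. This is not an omitted detail but a stated response variable that the article's own schedule and instrument rule out.

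**Conclusion.** The point holds as a contradiction in the response variable of the sole confirmatory analysis. One version, the total score at 1, 4 and 12 months, is computable and consistent with the outcome definition and the sample size calculation. The other, change from baseline, cannot be computed. It should be corrected because the sentence that specifies the MMRM response names the impossible version.

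No loss of power can be assigned to the plan. If the total score is used, the design is unaffected, with a detectable difference of 8.18 to 8.25 points. If a 1-month baseline were substituted, any effect already present at 1 month would be lost from the contrast. The size of that loss is unknown, because the documents give neither the 1-month effect nor the correlation between visits. The conclusion rests on Table 2 being the complete schedule for the behaviour survey.

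**What to change.** Delete both change-from-baseline sentences and state one primary analysis:

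- **Response:** total questionnaire score at 1, 4 and 12 months after delivery.
- **Model:** MMRM with arm, visit, arm-by-visit interaction and the season stratum used in randomization (winter or other), keeping the stated covariance structure and fallback sequence.
- **Primary contrast:** arm difference at 4 months, two-sided 5%.
- **Clarification:** the 1-month score is an outcome and is not used as a baseline, because subtracting it would remove any effect already present at that visit.

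The cost is wording, plus the ethics committee approval that the article requires for amendments. The edit should be made before outcome data are examined by arm. No new data collection, visit or change in sample size is needed.

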### Secondary outcomes

#### Incidence and severity of atopic dermatitis and eczema infantile

The incidence of infantile AD and eczema infantile is compared between groups at all time points using Pearson’s chi-squared test. The severity of these diseases is compared between groups using descriptive statistics of scores at each time point. Subgroup analyses are performed to assess the incidence and severity of AD related to the amount and frequency of moisturizer used during the study and the skin condition of infants.

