#### Secondary objectives

The secondary objectives are as follows:
To determine whether the use of a moisturizer can reduce the onset of AD and eczemaTo determine whether the onset of other atopic disorders can be prevented by the use of a moisturizerTo examine the association between the onset of AD and food allergy sensitizationTo establish the safety of the recommended moisturizer in neonatesTo investigate the presence of allergies, skin condition, serum immunoglobulin E (IgE), and thymus and activation-regulated chemokine (TARC) levels in neonates

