### Trial design

This study is an assessor-blinded, randomized controlled, parallel-group comparison study (comparing our educational program group with an established childbirth education group) conducted in Chiba Aiyu-kai Kinen Hospital (hereafter referred to as “our hospital”) to examine the superiority of the educational program over established programs. Subjects are randomized in a 1:1 ratio into one of the two groups. The participants and study personnel are not blinded with respect to the assignments.

This protocol is written in accordance with the Standard Protocol Item: Recommendations for Interventional Trials (SPIRIT) guideline. Trial registration is through the University Hospital Medical Information Network – Clinical Trials Registry (UMIN-CTR) (UMIN000034730).

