#### Secondary outcomes

We set the following seven secondary outcomes:
Incidence and severity of atopic dermatitis and eczema infantile

The incidence and severity of AD and eczema in infants aged 1 week, 1 month, 4 months, and 12 months are determined by a “blinded” pediatrician according to the Clinical Practice Guidelines for the Management of Atopic Dermatitis 2016 prepared by the Japanese Dermatological Association: URL:https://www.dermatol.or.jp/uploads/uploads/files/guideline/atopicdermatitis_guideline.pdf.
2.Incidence of food allergy and sensitization to egg white, milk, and ovomucoid

The incidence of food allergy in infants aged 4 and 12 months is determined by sensitization using serum antigen-specific IgE [49], medical interview, and oral food challenge or a clear history of allergy triggered by accidentally ingested foods
3.Analysis of stratum corneum hydration, transepidermal water loss (TEWL), and microscopic and digital images

Stratum corneum hydration in infants is measured three to five times on the left lower leg, forehead, and left cheek using Skicon-200EX® (IBS Japan Co., Ltd., Shizuoka, Japan). TEWL is determined two to three times on the left lower leg, forehead, and left cheek using the VapoMeter® (DelfinTechnologies, Kuopio, Finland). Enlarged images of the skin of the left lower leg, forehead, and left cheek in infants are acquired using a USB microscope M3 (Scalar Corporation, Tokyo, Japan). Images of a wide range of skin surfaces in infants are obtained using a digital camera (Canon, Tokyo, Japan). The skin is measured and photographed at 22 °C and 50% humidity.
4.TARC level

Serum TARC level is measured in infants aged 4 and 12 months to assess the severity of AD
5.Frequency of use and amount of moisturizer

The total amount of moisturizer used during the study is calculated to predict the effect of the educational program. The moisturizer is provided free of charge to those who want to use it
6.Questionnaire survey on living habits, awareness, and knowledge of mothers before and after pregnancy

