### Randomization procedure and concealment of allocation

Participants who meet the eligibility criteria and agree to participate in the study are randomized after signing the informed consent form. These subjects are stratified according to the estimated delivery date into winter and other seasons, and randomized using the permuted-block method. A statistical analyst generates a random allocation code using R statistical software (R Foundation for Statistical Computing) to randomize the subjects at each investigational site. The study is an assessor-blinded trial, and all raters are blinded with respect to the assignments. Also only the statistical analyst is aware of the stratification block size; the remaining staff is blinded. Subjects are randomized in a 1:1 ratio into one of two groups.

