#### Incidence of food allergy and sensitization to egg white, milk, and ovomucoid

The rate of sensitization to each allergen is compared between groups with a cut-off value of the incidence of food allergy and the serum antigen-specific IgE level (equal to or more than class II) in infants at each time point using Pearson’s chi-squared test. Subgroup analysis is performed to assess the outcomes related to the amount and frequency of moisturizer used during the study and the onset of AD in infants.

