## Appendix

**Table 3 Tab3:** Self-evaluation of questionnaire at 4 months after delivery

Question	Options				
How often do you vacuum the bed pad?	Never	Once a month	Once a week	2 or 3 times a week	Every day
How often do you wash the bedclothes?	Never	Once a month	Once a week	2 or 3 times a week	Every day
Are there any smokers living together? If yes, where do they smoke?	Yes Any place	Yes Under a ventilator	Yes Only outside the room	Yes Only outside the home	No one at all
Do you smoke? If yes, how often do you smoke?	Yes Frequently	Yes Often	Yes Sometimes	No But used to smoke	No Never smoked
How long are you be exposed to sunlight?	Not at all	Less than 30 min a day	30 min to 1 h a day	1 to 2 h a day	2 h or more a day
How often do you use sunscreen?	Never	Rarely	Sometimes	Everyday	2 times a day
How often do you take your baby outside?	Never	As long as possible	As short as possible	Not conscious	Short time with conscious
How often do you eat fish?	Less than once a week	1 or 2 times a week	3 or 4 times a week	5 or 6 times a week	Every day
How often do you eat eggs?	Less than once a week	1 or 2 times a week	3 or 4 times a week	5 or 6 times a week	Every day
How often do you eat meat?	Less than once a week	1 or 2 times a week	3 or 4 times a week	5 or 6 times a week	Every day
How often do you eat mushrooms?	Less than once a week	1 or 2 times a week	3 or 4 times a week	5 or 6 times a week	Every day
How often do you eat foods containing *Lactobacillus*?	Less than once a week	1 or 2 times a week	3 or 4 times a week	5 or 6 times a week	Every day
How often do you eat seaweeds?	Less than once a week	1 or 2 times a week	3 or 4 times a week	5 or 6 times a week	Every day
How often do you use soap when bathing your baby?	Less than once a week	1 or 2 times a week	3 or 4 times a week	5 or 6 times a week	Every day
How often do you wash your baby with a lathered soap?	Never	Rarely	Sometimes	Frequently	Always
How do you wash your baby’s face?	With hot water	Wear with gauze	Only cheeks or round mouth with soap	Whole face with soap but avoiding eyes	Whole face with soap
How do you wash your baby’s body?	Not at all	With hot water	Wear with gauze	Whole body with soap but avoiding eyes	Whole body with soap
How often do you use moisturizer for your baby?	Never	Rarely	Serious skin problems occur	Any skin problems occur	Every day
How much moisturizer do you use for your baby?	Not at all	Rubbing	Thinly	Thinly or plenty depend on body part	Plenty

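### Two secondary objectives ask whether moisturizer prevents AD and other atopic disorders, but the only analyses that address them are subgroups by self-selected use after randomisation, which cannot be read causally

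*Protocol article*

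**What the plan says.** Under Secondary objectives, the first aim reads "To determine whether the use of a moisturizer can reduce the onset of AD" and eczema. The second asks in the same causal terms whether moisturizer prevents other atopic disorders.

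What is randomised is education. Trial design describes the study as "comparing our educational program group with an established childbirth education group", and the randomisation section adds: "Subjects are randomized in a 1:1 ratio into one of two groups". Moisturizer is outside the allocation. Secondary outcomes, item 5, says: "The moisturizer is provided free of charge to those who want to use it". Table 1 shows that the programme teaches washing and moisturizing and sets out to promote adherence to skin care.

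For AD and eczema, the analysis section plans a chi-squared comparison between groups. It then plans subgroup analyses to "assess the incidence and severity of AD related to the amount and frequency of moisturizer used during the study" and by the skin condition of the infants. For food allergy and sensitization, subgroup analysis is to "assess the outcomes related to the amount and frequency of moisturizer used during the study and the onset of AD in infants".

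On measuring use, Secondary outcomes states: "The total amount of moisturizer used during the study is calculated to predict the effect of the educational program". Table 2 schedules provision at discharge, 1 month and 4 months, and container collection at 1, 4 and 12 months.

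**The concern.** The question asked and the comparison planned do not match. The between-arm test is protected by randomisation, but it compares a package covering diet, smoking, bedding, sunlight and skin care with the control condition. It cannot isolate moisturizer. The moisturizer objectives therefore rest on the subgroup analyses, where mothers choose the exposure after randomisation, partly under the influence of the allocated arm and possibly in reaction to the infant's skin.

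An apparent harm could simply reflect heavier use in infants who already had eczema. An apparent benefit could reflect more health-conscious families or infants with healthier skin. Either could be reported as the answer to a stated objective, and the Discussion foresees publicising the programme as a preventive approach if it works.

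**Working it through.** The plan states no figure on this point, so there is none to reproduce. The check has two parts: timing and selection as the document gives them, then an illustration of how far the crude comparison can move.

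**Timing and selection**

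- Secondary outcomes has AD and eczema assessed at 1 week and at 1, 4 and 12 months. Moisturizer is supplied up to 4 months and containers are collected up to 12 months. Use during the study can therefore include use after eczema has appeared.
- In the Appendix questionnaire, one of the two moisturizer-frequency items has five options, two of which are triggered by skin trouble. One is "Any skin problems occur"; the other refers to serious skin problems. The trial's own instrument thus anticipates reactive use.
- The word subgroup allows two readings. Comparing heavier with lighter users is confounded by self-selection. Comparing arms within levels of use conditions on a variable that the intervention is meant to change. Neither gives the causal effect of moisturizer.

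**Illustration**

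All inputs are assumptions, because the document gives no AD or usage rates:

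- q = 0.30 of infants have an early skin problem.
- AD risk is r1 = 0.40 with an early problem and r0 = 0.10 without.
- u1 and u0 are the proportions of higher users with and without an early problem.
- RR is the true effect of higher use.

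Formulas:

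- H = q·u1 + (1−q)·u0
- AD risk in higher users = RR·[q·u1·r1 + (1−q)·u0·r0] / H
- AD risk in lower users = [q·(1−u1)·r1 + (1−q)·(1−u0)·r0] / (1−H)

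Example with RR = 1, u1 = 0.90, u0 = 0.40:

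- H = 0.27 + 0.28 = 0.55
- Higher users: (0.108 + 0.028)/0.55 = 0.247
- Lower users: (0.012 + 0.042)/0.45 = 0.120
- Crude ratio: 0.247/0.120 = 2.06

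Example with healthier infants as the heavier users, RR = 1, u1 = 0.40, u0 = 0.70:

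- H = 0.12 + 0.49 = 0.61
- Higher users: (0.048 + 0.049)/0.61 = 0.159
- Lower users: (0.072 + 0.021)/0.39 = 0.238
- Crude ratio: 0.67

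| u1 / u0 | Crude ratio if true RR = 1.00 | Crude ratio if true RR = 0.70 |
|---|---|---|
| 0.50 / 0.50 | 1.00 | 0.70 |
| 0.60 / 0.40 | 1.30 | 0.91 |
| 0.70 / 0.40 | 1.49 | 1.05 |
| 0.80 / 0.40 | 1.73 | 1.21 |
| 0.90 / 0.40 | 2.06 | 1.44 |
| 0.40 / 0.70 | 0.67 | 0.47 |

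Among these scenarios, the true value is recovered only where use is unrelated to early skin problems.

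An extreme case treats eczema and AD as the same event, with no true effect and high use in 80% of affected and 50% of unaffected infants:

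- AD risk 30%: 0.24/0.59 = 0.407 against 0.06/0.41 = 0.146, ratio 2.78.
- AD risk 15%: 0.12/0.545 = 0.220 against 0.03/0.455 = 0.066, ratio 3.3.

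These mark what a very tight link between use and AD would do. They are not expected values.

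**The case against.** The strongest defence has five parts.

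- **The randomised comparison is there.** The AD section opens with the between-arm test, and analyses follow intention-to-treat in general. This stands, but that test answers the education question.
- **The limitation is conceded.** The Discussion accepts that the trial may not give clear data on individual measures because mothers choose them. This is true in general terms, but the objectives and analyses are unchanged. Elsewhere the article does use weaker wording: the third secondary objective is framed as an association and the skin-image work as exploratory. The moisturizer objectives carry neither label.
- **Exposure windows and adjustment belong in a fuller document.** Their absence alone is not the point, and containers collected at successive visits would allow use by interval. What the article does state is a causal objective paired with subgroups by use during the study, and that pairing needs correcting. The additional split by skin condition is no cure, since nothing says at which visit it applies or whether it is combined with use.
- **The questionnaire does not show that heavy users are mainly reactive.** Correct. The skin-problem options score 3 and 4, below daily use at 5, and the second frequency item has no such trigger. The instrument shows that reactive use is expected, not that it dominates.
- **Food allergy split by onset of AD.** A reader might infer that this is a further fault of the same kind. The document does not support that: the split serves the separate third objective, which is already worded as an association.

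**Conclusion.** The point holds as a mismatch between objective and analysis. The first two secondary objectives cannot be answered causally by subgroups of self-selected use after randomisation.

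The direction and size of the bias cannot be derived from the document. Under the assumed inputs, a null effect appears as a ratio of about 0.67 to 2.06, and a true 0.70 as about 0.47 to 1.44, so a real benefit could look like harm.

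A reader might infer that the plan will make moisturizer look harmful, with ratios near 3. That needs eczema and AD to be the same event and use to be mainly reactive, and the document establishes neither. A reader might also infer that the trial's AD results as a whole are compromised. They are not: the between-arm comparison and the primary outcome are untouched, and the article calls no AD analysis confirmatory.

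**What to change.** 1. Reword the first two secondary objectives as exploring the association between moisturizer use and AD, eczema and other atopic disorders.
2. State that the between-arm comparison is the only randomised evidence on AD, and that it estimates the effect of the education package.
3. Label the moisturizer-use analyses observational and exploratory.
4. Define exposure before outcome. One acceptable option is a landmark analysis: container use from discharge to 1 month, in infants free of eczema at 1 month, with AD at 4 and 12 months as outcome, adjusted for family allergy history and the season stratum. Other time-ordered analyses would also serve.

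The landmark option needs no new data collection. Table 2 already schedules containers and skin findings at 1 month and AD diagnosis at 4 and 12 months, family allergy history is a baseline item, and season is a stratification factor.

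The costs are an amendment to protocol wording, which the protocol requires to go to the ethics committee; fewer infants in the exploratory analysis, from a target of 120 women; and a weaker claim. Confounding by self-selection would remain, so the result would still be an association.
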